#### Secondary Outcome

##### Influenza Vaccine Outcomes

We will perform a descriptive analysis, calculating the percentage of patients for whom self-report through our intervention was the sole method for documentation of influenza vaccination completion. We will assess this at the end of the 2014-15 influenza season. This analysis is intended to provide preliminary insights into the percentage of patients who are vaccinated outside of the RMG clinics and who choose to self-report these vaccines.

#### Process Measures

We will examine patients who receive portal messages and calculate (1) percentage of recipients who open messages and (2) percentage of recipients who complete questionnaires. We will examine patients who receive IVR calls and calculate (1) percentage of recipients who answer the call and (2) percentage of recipients who complete the calls by responding to questions.

### Proposed Analyses

To determine the impact of our interventions on RMG vaccination rates for the 2014-15 influenza season, we will perform unadjusted and adjusted analyses of randomized patients (30,000 patients). Because of differential rates of vaccination at baseline between portal users and nonusers, analyses in these groups will be conducted separately. Intention-to-treat unadjusted chi-square analyses will include the analyses presented in Table 1.

We will examine the adequacy of randomization in the overall group and separately among e-portal users and non e-portal users by assessing whether there was differential representation in the intervention versus control groups by 5 patient characteristics readily available in the EHR. These will include (1) age group; (2) race/ethnicity; (3) sex; (4) influenza vaccination in previous year; and (5) completion of an office visit in the previous year; if differences are found we will carry out adjusted analyses using logistic regression to control for significant differences, modeling odds of receiving influenza vaccine.

Multivariate logistic regression analyses will also be performed. As in our unadjusted analyses, due to differential rates of vaccination at baseline between portal users and nonusers, adjusted analyses in these groups will be conducted separately. We will create dummy variables for assignment to the portal message arm (among portal users) and for assignment to the IVR call arm (among both portal users and, separately, among nonportal users). Including these dummy variables and adjusting for demographic and practice-level covariates, we will model odds of receiving an influenza vaccine in the 2014-15 influenza season. We will also examine the heterogeneity of treatment effects within each subgroup using logistic analysis.

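### One adjusted analysis picks its covariates by baseline significance tests, and prior-year vaccination and prior-year office visit are named only under that rule

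*Protocol article*

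**What the plan says.** The Proposed Analyses section of the protocol article sets out three layers.

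- **Unadjusted tests.** "Intention-to-treat unadjusted chi-square analyses will include the analyses presented in Table 1".
- **Balance check with conditional adjustment.** The plan looks for "differential representation in the intervention versus control groups by 5 patient characteristics readily available in the EHR", and does so "in the overall group and separately among e-portal users and non e-portal users". The five are age group, race/ethnicity and sex, followed by "4) influenza vaccination in previous year; and (5) completion of an office visit in the previous year". The consequence of the check is that "if differences are found we will carry out adjusted analyses using logistic regression to control for significant differences".
- **Always-run model.** "Multivariate logistic regression analyses will also be performed", separately in portal users and nonportal users. Its content is given as "Including these dummy variables and adjusting for demographic and practice-level covariates".

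Prior-year vaccination and prior-year office visit appear in the second layer only. Neither is a demographic or a practice-level variable in the ordinary sense of those words.

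**The concern.** The Randomization Approach section assigns patients by a computerized method. If that is carried out correctly, a significant baseline difference is a chance event. A baseline p-value measures how uneven a variable happens to be. It does not measure how strongly the variable predicts the outcome, which is what determines the value of adjusting for it. The rule also leaves the existence and content of the second-layer analysis to the data.

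For age group, race/ethnicity and sex this matters little, because the always-run model would normally cover them as demographics. For prior-year vaccination and prior-year office visit the trigger is the only route into a model that the text gives. Past vaccination behaviour is likely to be among the best available predictors of vaccination this season. At stake is power and precision in the adjusted analysis, obtainable from variables that the plan itself describes as easy to extract.

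**Working it through.** **1. The plan's own figure.** The Power and Sample Size section gives 4286 per arm for 80% power, a 3% improvement (read as 3 percentage points) and two-sided α = 0.05. The baseline rate is not stated, so it was back-solved. With 42% v 45%, pooled variance and no continuity correction:

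n = [1.960 × √(2 × 0.435 × 0.565) + 0.8416 × √(0.42 × 0.58 + 0.45 × 0.55)]² / 0.03² = (1.374 + 0.590)² / 0.0009 ≈ 4286.

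This matches, but 42% is an assumption (55% v 58% gives the same n). The figure is for an unadjusted comparison, so nothing below changes it.

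**2. How often the trigger fires by chance.** The level of the baseline tests is not stated; 0.05 and independent tests are assumed.

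- One given variable, one comparison: 5% (4.7% in a simulation of 40,000 trials). About 95% of the time it is not adjusted for.
- At least one of 5 tests: 1 − 0.95⁵ = 22.6%.
- At least one of 10 (two populations): 1 − 0.95¹⁰ = 40.1%.
- At least one of 15 (adding the overall group): 1 − 0.95¹⁵ = 53.7%. This is an upper figure, because the overall group overlaps the other two.

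**3. Effect on type I error.** The simulation assumed 5000 per arm, 40% vaccinated the previous year, and 60% v 20% vaccinated this season by prior-year status. Type I error was 5.1% for the unadjusted test and 4.7% for test-then-adjust, so there is no inflation.

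**4. What prior-year vaccination could be worth.** The documents give no association between prior-year and current vaccination, so all rates here are assumed. With f the proportion vaccinated the previous year, r1 and r0 this season's rates in those with and without it, and p = f·r1 + (1 − f)·r0:

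R² = f(1 − f)(r1 − r0)² / [p(1 − p)]; equivalent extra patients per arm = 5000 × R² / (1 − R²).

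| f | r1 | r0 | p | R² | Patients per arm |
|---|---|---|---|---|---|
| 0.30 | 0.20 | 0.08 | 0.116 | 0.029 | about 150 |
| 0.35 | 0.25 | 0.05 | 0.120 | 0.086 | about 470 |
| 0.30 | 0.30 | 0.05 | 0.125 | 0.120 | about 680 |

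The first and last rows are the extremes for f of 30-50%, r1 of 20-30% and r0 of 5-8%.

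**5. Sensitivity to the overall rate.** The rates in step 4 imply 9.5-19% vaccinated overall (0.3 × 0.20 + 0.7 × 0.05 = 0.095; 0.5 × 0.30 + 0.5 × 0.08 = 0.19), well below the back-solved 42%. A wider grid, with overall rates of 13-40%, gave R² from about 0.02 to 0.29, a reduction in the SE of the risk difference of about 1-15%. In the simulation of step 3 (R² about 0.17) the SD of the risk difference fell from 0.0096 to 0.0088, about 8%. At 42% v 45% and 5000 per arm, power rises from 85.7% to 86.4%, 87.4% and 89.1% for R² of 0.02, 0.05 and 0.10.

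**6. The odds-ratio scale.** A logistic simulation (300 trials; half vaccinated the previous year; control rates 64% v 20%, so 42% overall) gave a mean SE of the log odds ratio of 0.040 unadjusted and 0.045 adjusted. The mean estimate moved from 0.118 to 0.148, and mean z rose from 2.91 to 3.27. On this scale the gain is power, not a narrower interval.

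**The case against.** The strongest reply has four parts.

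- **The always-run model is not conditional.** A reader might infer that all covariates enter only if flagged, or that every adjusted result hangs on chance. The text does not support this: the third layer is fitted regardless and would normally include age, race/ethnicity and sex. The objection stands, and limits the point to the second layer and to the two variables named only there.
- **The main tests are untouched.** A reader might infer that the trial's main conclusion or its error rate is at risk. The Table 1 chi-square tests are run whatever the balance check shows, and step 3 finds no inflation. This stands in full.
- **Chance imbalance is not bias.** With 35% vaccinated the previous year, a just non-significant imbalance of 1.9 SE is 1.9 × √(2 × 0.35 × 0.65 / 5000) = 1.8 points. With a 20-point gap between strata it shifts the risk difference by 0.36 points. That may look like an uncorrected bias, but it is random error already contained in the unadjusted SE, which is √(2 × 0.12 × 0.88 / 5000) = 0.65 points at 12% overall. The shift is about half of one SE, in a near-worst non-significant case. This stands.
- **The article is condensed.** A full covariate list for the always-run model may sit in a document not shown, and its brevity here is not an error. That is right, but it does not reach the trigger. The trigger is an explicit selection rule, and a longer covariate list elsewhere would leave it in place.

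**Conclusion.** The concern holds in limited form. One supplementary adjusted analysis selects its covariates by baseline significance in a randomized trial, which is a poor rule. As written, prior-year vaccination and prior-year office visit reach a model only through it, about 5% of the time per comparison at an assumed 0.05 level.

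The cost is power and precision in the adjusted analysis, not validity of the main tests. The direction is sound if prior-year vaccination predicts current vaccination. The size rests wholly on assumed rates: R² of about 0.03-0.12, or about 150-680 patients per 5000-patient arm, under the rates in step 4, and a wider range if overall vaccination is nearer the level implied by the sample size. The change is worth making because it costs almost nothing, not because the present plan would mislead.

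**What to change.** Delete the significance-test trigger and keep the comparison of the five characteristics as a descriptive baseline table. In the always-run logistic model, prespecify within portal users and within nonportal users: the arm indicators, age group, race/ethnicity, sex, prior-year influenza vaccination and prior-year office visit, together with the planned practice-level covariates, whatever imbalance is observed.

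A standardized risk difference with its confidence interval can be reported beside the odds ratio, so that the precision gain is visible. The unadjusted chi-square can stay as the main test; replacing it would be a preference, not a correction.

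The cost is wording. The plan already intends to extract all five variables, and no sample-size figure changes. One small addition is needed: a rule for missing race/ethnicity, such as an unknown category. Because the abstract reports that analysis is already under way, the change should be dated, with a statement of whether results by arm had been seen.

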### Power and Sample Size

With our proposed sample size and using a factorial design, power calculations using baseline vaccination rate estimates indicated that 4286 participants per arm would give 80% power to detect a 3% improvement in influenza vaccination rates between groups (α=.05; 2-sided). Based on previous studies [29,30], we expect a 10-20% improvement in vaccination rates for either intervention compared with control.

**Table 1 table1:** Analyses by arm.

Study question	Comparison
Among portal users, did portal message receipt alone increase the likelihood of influenza vaccine completion compared with control?	Compare percentage of vaccine completion among those randomized to receipt of portal messages versus those randomized to neither portal messages nor IVR calls (usual care). (Arm 2 vs 4)
Among portal users, did portal message receipt plus IVR call increase the likelihood of influenza vaccine completion compared with portal message alone?	Compare percentage of vaccine completion among those randomized to receipt of both portal messages and IVR calls versus those randomized to only portal messages. (Arm 1 vs 2)
Among portal users, did IVR call alone increase the likelihood of influenza vaccine completion compared with control?	Compare percentage of vaccine completion among those randomized to receipt of IVR calls versus those randomized to neither portal messages nor IVR calls (usual care). (Arm 3 vs 4)
Among those who do not use portals, did IVR call alone increase the likelihood of influenza vaccine completion compared with control?	Compare percentage of vaccine completion among those randomized to receipt of IVR calls versus those randomized to neither portal messages nor IVR calls (usual care). (Arm 5 vs 6)

## Results

Intention-to-treat unadjusted chi-square analyses will be performed to assess the impact of portal messages, either alone or in combination with the IVR call, on influenza vaccination rates.

## Discussion

This study will test the effectiveness of a patient-directed CDS intervention, aimed at improving rates of influenza vaccination within a primary care adult population. The approach described has important implications for future patient-directed CDS initiatives seeking to use tethered patient portals. As a low-cost and rapid means of communicating with patients who have activated their electronic accounts, patient portals are a promising channel through which CDS may be delivered. Targeting patients through portals aligns well with the “CDS Five Rights,” which stipulate that effective CDS delivers the right information to the right people, via the right channels, in the right intervention formats and at the right points of workflow [31]. Our approach studies the possibility that the patient is the person best positioned to receive and act on information related to influenza vaccination.

Influenza vaccination has several characteristics that made it ideally suited for this study design. Influenza vaccinations are a single-dose annual vaccine, for which standing orders were already in place in our medical group. They are recommended almost universally across age groups, and therefore, we did not require that physicians review the list of patients to whom promotional messages were directed prior to sending, thereby reducing physician burden. There is widespread familiarity with influenza vaccination among the lay public, and numerous community sites and workplaces offer these vaccinations, thus they are commonly administered outside of the medical group. Seeking to collect data on vaccinations given in the community was therefore a reasonable component of our outreach. This factor might be less appropriate for other preventive health behaviors. Guidelines calling for annual vaccination create a short recall period (2-3 months in our study design) for individuals reporting vaccination in a given season. The short recall period and widespread familiarity was our rationale for accepting patient self-report. With inputs from the physicians on our research team, we further reasoned that providers would be willing to update the EHR based on patient self-report of influenza completion during an in-person visit (without accompanying printed documentation) and that our collection of self-reported data via outreach was an acceptable alternative to in-person patient report. Our outreach may have the additional benefit of identifying patients with influenza vaccine allergy that has not previously been documented.

This protocol has some limitations. Although we collected self-report of influenza vaccinations completed in the community, our primary analysis focuses on RMG-documented vaccines, thus avoiding the bias that would be introduced through differential capture (intervention versus control) of self-reported data.

For our secondary outcome measurement, we will report percentage of patients self-reporting influenza vaccines completed in the community. Although self-report introduces the possibility for inaccuracies, self-reported vaccination status is a measure commonly used to assess vaccination status and is the standard used by the Behavioral Risk Surveillance System and the National Health Interview Survey [32-34]. Previous validation efforts for self-reported influenza vaccines documented high sensitivity (0.98 to 1.0) and moderate specificity (0.71-0.79) [32]. In addition to reviewing commonly accepted measures and published validation reports, we also considered the levels of ascertainment consistent with routine clinical care. Many clinicians accept a patient’s verbal self-report of completed influenza vaccination and update the EHR accordingly (without requiring paper documentation). For all of these reasons, we chose to allow patient self-reported influenza vaccinations to be entered into the EHR.

An additional limitation of our study stems from the timing of outreach. After eligibility determination but prior to disseminating the outreach, we will have a 1-week gap built in for quality checks and data transfers to the company handling IVR calls. It is possible that during this 1-week gap, patients randomized to receipt of the intervention will obtain their influenza vaccines. Patients with vaccinations completed during this period should be evenly distributed across all arms, minimizing any associated bias. Once the intervention starts, IVR calls and patient portal messages will be disseminated in batches. While this is a standard protocol for delivering IVR appointment reminders and prevents outgoing portal messages from being labeled as spam by email servers, it also introduces the possibility that additional patients may get vaccinated prior to receiving the intervention. Again, patients vaccinated prior to receipt of messages should be evenly distributed across all arms.

While our single-site study is limited insofar as it cannot be considered representative on a national scale, a future study could address this by sampling from our population in proportion to national demographics. In addition, we have designed our intervention to be easily tested across diverse settings. This intervention will be implemented using Epic, one of the top EHR vendors in the country [35]. If successful, this study’s intervention may be adapted by other large health care organizations using Epic and tested as a means of increasing vaccination rates among diverse populations.

## Appendix

Multimedia Appendix 1 Portal message example.

## Abbreviations

CDS: clinical decision support
EHR: electronic health record
IRB: Institutional Review Board
IVR: interactive voice recognition
RMG: Reliant Medical Group
